#### MRI analyses

Whole-brain and hippocampal volume and cortical thickness will be accessed using the FMRIB Software Library (FSL) vertex-based analysis and FreeSurfer Image Analysis Suite, respectively. White matter integrity is assessed with tract-based spatial statistics.

Resting state and task-based functional MRI (fMRI) data will be preprocessed and analyzed with the FMRIB Expert Analysis Tool (FEAT; latest version available at trial completion) part of FMRIB’s Software Library (FSL; www.fmrib.ox.ac.uk/fsl). For resting-state fMRI data, we will use Multivariate Exploratory Linear Optimized Decomposition into Independent Components (MELODIC) to conduct group-level ICA by multi-session temporal concatenation, identifying the common resting state networks across the groups. Furthermore, fMRI data from the N-back working memory task and the grocery list encoding and retrieval tasks will be analyzed using a region-of-interest analysis to assess differences between the intervention and control groups in neural activity in the dorsal PFC (dPFC) after completing 4 weeks of treatment (adjusting for any difference in neural activity at baseline). We will also conduct volume-of-interest analyses of the dPFC for the N-back task and for both the dPFC and hippocampi for the word encoding task to investigate our hypotheses. Finally, exploratory whole-brain analyses will be conducted to investigate any treatment-related effects in other brain regions.

#### Positron emission tomography analyses

Dynamic [^11^C]UCBJ-J PET imaging will be acquired over 90 min using the High Resolution Research Tomograph (HRRT; CTI/Siemens, Knoxville, TX, USA) PET scanner as previously described [72]. Following motion-correction, the PET data are processed using the PVElab software pipeline (https://nru.dk/index.php/allcategories/category/30-software), or similar, where PET images are co-registered to participants’ T1-weighted 3 T MR image, and regions of interest are automatically delineated [73].

Radioactivity concentrations are extracted from grey matter to generate regional time-activity curves (TACs) and subsequently used for kinetic modeling. Quantification is performed using the simplified reference tissue model 2 (SRTM2) with the white matter region centrum semiovale as pseudo-reference tissue. The outcome is the non-displaceable binding potential (BP_ND_; ratio of specifically bound radioligand to that of non-displaceable radioligand in tissue).

### Sample size and power calculation

Power calculations were performed with the software program G*Power 3.1.9.4 [74] and were based on the primary hypothesis that altitude-like hypoxia combined with cognitive training produces robust sustained cognitive improvement compared with normoxia and no training (hypothesis i). As hypoxia triggers the endogenous production of EPO, we based the power calculation on our previous clinical study of subcutaneous EPO treatment in which we demonstrated clinically relevant cognitive enhancement [75]. In that study, the differential change between EPO and placebo groups in the same cognitive composite score as we apply in the present study was 0.5 standard deviations (SD) [75]. Assuming an effect of 0.4 SD differential change (medium effect size) between the two groups and 0.5 SD of the change, we will achieve > 80% power to detect an effect at an alpha level of 0.05 by including 26 participants per group. This number of participants provides adequate power for the structural and functional MRI investigations based on our previous studies of EPO [30, 32, 33]. To accommodate for up to a 20% drop-out, we will include 30 participants per treatment arm; i.e., 120 participants in sub-study 1 and 60 patients in sub-study 2.

For PET imaging of SV2A [^11^C]UCB-J binding (reflecting presynaptic density), power calculations involved the following assumptions: (i) the average (SD) *BP*_ND_ in the frontal cortex in healthy participants is 3.36 (0.38) (based on in-house data), and (ii) the combined intervention will lead to a 10% increase in *BP*_ND_. With these assumptions, we will achieve a power of 0.82 to detect an effect at significance level of 0.05 post-treatment of the combined intervention (primary aim) with *n* = 20 per treatment arm using a two-tailed, independent-sample *t*-test.

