**Methods:**

In sub-study 1, 120 healthy participants are randomized to one of four treatment arms in a double-blind manner, allowing for examination of separate and combined effects of three-week repeated moderate hypoxia and cognitive training, respectively. In sub-study 2, 60 remitted patients with major depressive disorder or bipolar disorder are randomized to hypoxia with cognition training or treatment as usual. Assessments of cognition, psychosocial functioning, and quality of life are performed at baseline, end-of-treatment, and at 1-month follow-up. Functional magnetic resonance imaging (fMRI) scans are conducted at baseline and 1-month follow-up, and [^11^C]UCB-J positron emission tomography (PET) scans are performed at end-of-treatment to quantify the synaptic vesicle glycoprotein 2A (SV2A). The primary outcome is a cognitive composite score of attention, verbal memory, and executive functions. Statistical power of ≥ 80% is reached to detect a clinically relevant between-group difference with minimum *n* = 26 per treatment arm. Behavioral data are analyzed with an intention-to-treat approach using mixed models. fMRI data is analyzed with the FMRIB Software Library, while PET data is quantified using the simplified reference tissue model (SRTM) with centrum semiovale as reference region.

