### Randomization and blinding

Randomization is conducted in the database program REDCap [51], which is also used to store the collected data, utilizing a 1:1 allocation ratio. Randomization occurs after inclusion of the participants planned to undergo treatment sessions together. Treatment groups are stratified for age (> 27 in sub-study 1 of generally young volunteers/ > 35 in sub-study 2 of patients). For randomization purposes, date of birth is registered to determine the stratum to which the participant belongs at the time of enrolment. Study identification numbers are given consecutively within each stratum and treatment arm. Randomization is conducted in the randomization module in REDCap, where an un-blinded researcher inputs the stratum and the program then retrieves the allocated intervention. To ensure blinding of the outcome-assessors, the randomization module in REDCap is only accessible to the researchers, who are not involved in evaluation of the efficacy parameters.

Healthy participants in sub-study 1 are blind to the oxygen condition since the low/normal oxygen air blown into the room is of equal temperature and humidity. Furthermore, they are told that they receive one of two forms of cognitive training, which effectively blinded participants in a previous study [52]. After study completion, we will assess whether blinding has been maintained for each participant, since there is a small risk that some participants develop symptoms of mild altitude sickness which could unblind them to their intervention. Blinding of the outcome assessors is ensured by their absence during the training visits (where oxygen levels are displayed and monitored on a screen outside the room). Participants will be instructed not to disclose any information concerning their intervention during outcome assessments and under no circumstances will the allocation be revealed to the outcome assessors. The training visits are conducted by researchers who are not involved in outcome assessments.

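### Thirty per arm does not cover 20% drop-out: it leaves 24, below the 26 the plan needs, and holds 26 only up to about 13% loss

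*Protocol article*

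**What the plan says.** Under Sample size and power calculation, the protocol article sets its inputs as follows: "Assuming an effect of 0.4 SD differential change (medium effect size) between the two groups and 0.5 SD of the change". From these it concludes that "we will achieve > 80% power to detect an effect at an alpha level of 0.05 by including 26 participants per group". The abstract repeats this and calls 26 per arm the minimum: "Statistical power of ≥ 80% is reached to detect a clinically relevant between-group difference with minimum" that number.

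The allowance for losses comes next: "To accommodate for up to a 20% drop-out, we will include 30 participants per treatment arm". This gives the recruitment targets, "120 participants in sub-study 1 and 60 patients in sub-study 2", that is, four arms of 30 and two arms of 30.

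The calculation is tied to hypothesis (i), hypoxia plus training against normoxia without training. The section Primary outcome measure defines the endpoint as change in the cognitive composite from baseline to week 4. Follow-up then continues to week 8.

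**The concern.** The figures 26, 30 and 20% stand in one paragraph and cannot all hold. If 26 per arm is the least that gives the intended power, an allowance for 20% loss must still leave 26, and 30 does not.

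What is at stake is the power of the primary comparison at an attrition level that the plan says it has provided for. Anyone relying on the sentence would believe the trial keeps more than 80% power with 20% loss. The same 26 and 30 are used in both sub-studies, so the error carries into both.

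**Working it through.** **Inputs (all from Sample size and power calculation unless noted).** Difference in change 0.4; SD of change 0.5; alpha 0.05; 26 per group required; 30 per arm enrolled; drop-out up to 20%. Allocation is equal (Randomization and blinding: "utilizing a 1:1 allocation ratio").

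**Assumption.** The section does not say whether the primary calculation is one- or two-sided. I take it as two-sided because 26 is exactly the two-sided minimum (below), and because the PET calculation in the same section is described as "using a two-tailed, independent-sample *t*-test".

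**Step 1: reproduce the plan's figure.** The standardised difference is d = 0.4/0.5 = 0.8. For a two-sample t-test with n per arm, the noncentrality parameter is d × √(n/2), on 2n − 2 degrees of freedom.

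- n = 26: 0.8 × √13 = 2.884, df 50, power 0.807
- n = 25: power 0.7915

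So 26 is the smallest number per arm that reaches 80%, and the plan's figure reproduces. A one-sided test would reach 80% with 21 per arm (0.8168, against 0.7994 at 20), so it is not what produced 26.

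**Step 2: apply the stated drop-out.**

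- Left after 20% loss: 30 × 0.80 = 24, below 26
- Largest loss that still leaves 26: (30 − 26)/30 = 13.3%
- Enrolment needed to cover 20%: 26/(1 − 0.20) = 32.5, so 33 per arm (4 × 33 = 132 and 2 × 33 = 66)
- The common shortcut of multiplying by 1.20: 26 × 1.20 = 31.2, so 32 per arm

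Neither way of inflating 26 for 20% gives 30.

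**Step 3: power by timing of the loss.** A 20% loss is 6 of 30 per arm. The section does not say when it occurs, so the number left at the week-4 assessment depends on how many leave before then.

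| Lost before week 4 (per arm) | Left at week 4 | Power |
|---|---|---|
| 6 | 24 | 77.4% |
| 4 | 26 | 80.7% |
| 3 | 27 | 82.2% |
| 0 | 30 | 86.1% |

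For n = 24 the noncentrality parameter is 0.8 × √12 = 2.771, on 46 degrees of freedom. The normal approximation gives 79.1% at 24, which is also below 80%.

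**The case against.** Four points can be made for the plan.

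*The 20% is an upper limit and may cover the whole study.* This stands in part. Participants who leave between weeks 4 and 8 still supply the primary endpoint, and if no more than four of the six losses per arm come before week 4, power does not fall below 80.7%. But the sentence does not restrict the 20% to late losses, so it is not true as a general allowance.

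*The mixed model keeps participants with incomplete data.* It does, but someone who leaves before week 4 contributes only a baseline value, which says very little about change to week 4. The stated calculation takes no credit for such participants.

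*Adjusting for baseline would recover the power.* A reader might infer this from the SD of change. If the composite had SD 1 at both visits, an SD of change of 0.5 would imply a correlation of 1 − 0.25/2 = 0.875 and a residual SD of √(1 − 0.875²) = 0.484. Power at 24 per arm would then be 79.97%. The documents give no correlation, and they define the composite as a sum of six z-scores, which does not have SD 1 by construction. Even if granted, the result reaches only about 80%. It does not rescue the sentence, and the model details may properly sit in the analysis plan.

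*The power claims themselves are correct.* This stands. Both the abstract and the 26-per-group statement are conditional on 26, and both reproduce.

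**Conclusion.** The drop-out sentence is wrong on the plan's own numbers. Thirty per arm tolerates about 13% loss before week 4, not 20%. If the full 20% is lost by then, power for the primary comparison is 77.4%, about 3 points below the 80.7% at 26. This rests on the stated difference and SD of change and on a two-sided test. It is a modest correction that should be made. It affects neither the type I error rate nor the definition of the endpoint.

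Three stronger readings are not supported:

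- **That the trial is underpowered as designed.** With no loss, 30 per arm gives 86.1%, and power stays above 80% up to 13.3% loss.
- **That the abstract's power statement is false.** It makes no claim about drop-out and is right for 26 per arm.
- **That every pairwise contrast in sub-study 1 falls short of a promised 80%.** The calculation covers only the combined intervention against normoxia without training. No power is claimed for the other contrasts, and hypothesis (iii) expects only small, transient effects of the single components.

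**What to change.** Replace the drop-out sentence in Sample size and power calculation with one of these:

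- *Thirty participants per arm allows for about 13% drop-out before week 4.*
- *Thirty participants per arm gives about 77% power if 20% are lost before week 4.*

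In either case, name the comparison meant: hypoxia plus training against normoxia without training in sub-study 1, and hypoxia training against treatment as usual in sub-study 2, to which the same 26 and 30 are applied. State that the loss is counted up to the week-4 assessment.

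The cost is one sentence and a slightly less favourable figure. The recruitment targets of 120 and 60 can stay, and the abstract needs no change. Only if the sponsor wants to keep the 20% allowance in full would the target have to rise to 33 per arm (132 and 66).

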**Fig. 1 Fig1:**
[figure not shown]
Overview of events across parallel sub-studies

Sub-study 1 involves four intervention groups: (1) normobaric hypoxia (12% O_2_) combined with cognitive training, (2) hypoxia (12% O_2_) with no training, (3) cognitive training under normoxia (20% O_2_), and (4) normoxia (20%) with no training in a double-blinded controlled design. This design enables us to disentangle combined and separate effects of altitude-like hypoxia and cognitive training. Participants are randomized in blocks and undergo interventions in these groups for practical reasons. During the three-week treatment, participants breathe 12% ambient oxygen (≈ 4400 m altitude) or approximately normal sea-level oxygen (20%) in a treatment room, 3.5 h daily, six days per week (18 sessions in total). After a blood test (days 1, 6, 20) and light standardized breakfast, they enter the treatment room. Here, they sit at a desk separated by desk dividers. On iPads, they perform cognitive training or matched control games without cognitive benefits. Cognitive training is interleaved by short breaks, during which the participants can relax or walk on a treadmill inside the room. This is to avoid complete physical inactivity throughout the 3.5 h sessions and thereby make the sessions more pleasant for participants. Participants undergo cognition assessments in weeks 1 (baseline), 4, and 8 and functional and structural MRI in weeks 1 and 8, when red blood cell counts are comparable between groups. Participants in the two extreme groups (normobaric hypoxia with cognitive training and normoxia with no training) will also undergo PET scanning in week 4 (post-treatment). Participants will be recruited consecutively for the PET scans until an equal distribution in each of the extreme intervention arms (i.e., hypoxia with cognitive training and normoxia with no training), sex, and age group is achieved.

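### The stated PET power of 0.82 does not follow from its own inputs, which give 0.78 with 20 participants per arm

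*Protocol article*

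**What the plan says.** The PET calculation is in the second paragraph of the Protocol article's section Sample size and power calculation. All its inputs are printed there:

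- The average binding potential (SD) "in the frontal cortex in healthy participants is 3.36 (0.38) (based on in-house data").
- The effect: "the combined intervention will lead to a 10% increase in" binding potential.
- The sample size and test: "20 per treatment arm using a two-tailed, independent-sample" t-test.
- The result and the error rate: "we will achieve a power of 0.82 to detect an effect at significance level of 0.05 post-treatment of the combined intervention".

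The same section names the software: "Power calculations were performed with the software program G*Power 3.1.9.4". Study design and procedure says that PET recruitment in sub-study 1 continues "until an equal distribution in each of the extreme intervention arms", so the two compared arms are of equal size. The schedule in Table 1 places PET at the end of treatment only. The PET paragraph gives no second SD, no correlation, no covariate adjustment and no drop-out allowance.

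**The concern.** A power statement that prints its mean, SD, effect, sample size, error rate and test can be checked completely, and this one does not reproduce. The discrepancy also crosses a threshold: the article presents the PET comparison as having more than 80% power, while its own inputs put it below 80%.

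This matters because SV2A binding is one of the measures on which hypothesis (ii) rests, and the power paragraph describes the post-treatment PET effect as the primary aim of that calculation. A reader weighing a non-significant PET result would credit the comparison with more sensitivity than the printed design has.

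**Working it through.** **Inputs** (all from Sample size and power calculation): mean 3.36, SD 0.38, increase 10%, n = 20 per arm, two-sided alpha 0.05, independent-sample t-test.

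**Check of the method on the primary outcome.** The same section assumes a difference of 0.4 with an SD of change of 0.5 and 26 per group, and claims more than 80% power. Here d = 0.4/0.5 = 0.8, and the exact (noncentral t) power of a two-sided t-test is 0.807. The claim reproduces, so the method matches the one the authors used there.

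**The PET calculation.**

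1. Difference: 0.10 × 3.36 = 0.336.
2. Standardised effect: d = 0.336/0.38 = 0.884.
3. Noncentrality: d × √(n/2) = 0.884 × √10 = 2.796.
4. Degrees of freedom: 2 × 20 − 2 = 38; two-sided 5% critical value 2.024.
5. Power: P(|T| > 2.024) for a noncentral t with 38 df and noncentrality 2.796 = **0.778**. The stated figure is 0.82, a gap of 4.2 percentage points.

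**Other readings, to see whether any gives 0.82 with 20 per arm.**

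| Reading | Power |
|---|---|
| Exact t-test, two-sided (as stated) | 0.778 |
| Normal approximation, two-sided: Φ(2.796 − 1.960) | 0.798 |
| Exact t-test, one-sided | 0.865 |
| Log scale | 0.738 to 0.741 |
| SD of treated arm also 10% larger | 0.736 |
| Mean 3.355 to 3.365 and SD 0.375 to 0.385 (rounding limits), 10% increase | 0.766 to 0.790 |

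The two-sided readings all fall short. The one-sided reading overshoots and contradicts the stated two-tailed test. A paired or baseline-adjusted analysis is not available, because PET is acquired once.

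**What would give 0.82.**

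- More participants at d = 0.884: 21 per arm gives 0.798, 22 gives 0.817 and 23 gives 0.835.
- A larger effect with 20 per arm: d = 0.933 is needed. At SD 0.38 that is a difference of 0.933 × 0.38 = 0.355, or 0.355/3.36 = 10.6% (10.55% before rounding).
- A smaller SD with 20 per arm and a 10% increase: 0.336/0.933 = 0.36.

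**A conditional point on the two regions.** Additional mechanistic outcome measures names both hippocampus and prefrontal cortex as PET regions of interest. If each were tested at 0.025, and if the frontal d of 0.884 held in both, power per region would be 0.68. The article fixes no such split and gives no hippocampal mean or SD, so this is an illustration only.

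**The case against.** The strongest reply does not dispute the arithmetic. It says that the slip is small and sits in a subordinate place. The cognitive composite is the primary outcome and PET is listed among the mechanistic measures. The 30 per arm come from the cognitive calculation, which reproduces. A gap of 4 points is also small beside the uncertainty in the 10% increase, for which the section gives no source. All of this stands, and it limits the practical weight of the point.

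The second reply is that 0.82 may be correct and one printed input wrong or rounded. If the 10% is a rounded value, an increase of 10.5% at the printed mean and SD gives 0.816, and an SD of 0.36 or 22 per arm would serve as well. That also stands: the article does not reveal the cause. It does not rescue the sentence, since the printed figures still disagree, but it does mean that the remedy should begin with the original calculation.

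Third, the 0.68 for two regions rests on an alpha split that the article does not propose, and the risk of over-reading a null PET result is a judgement, because the article does not say how such a result will be interpreted. Both are fair, and the conclusion depends on neither.

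**Conclusion.** The concern holds. With the mean, SD, increase, sample size, alpha and test as printed, the power of the PET comparison is 0.778, not 0.82. The type II error is 22% rather than 18%, and the comparison does not reach 80%. No two-sided independent-sample reading that was tried gives 0.82 with 20 per arm and a 10% increase. The result assumes that the printed inputs are the intended ones and that all 20 scans per arm are evaluable. The error is definite but modest in consequence: it affects a mechanistic outcome and leaves the cognitive primary outcome and its sample size untouched.

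**What to change.** Retrieve the original power run and compare its SD, percentage increase, sample size and result with the printed ones. Then do one of the following:

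- If the inputs are as printed, restate the power as 0.78 for 20 per arm, or say that 20 per arm gives power 0.82 for an increase of about 10.6%.
- If 22 per arm was intended, correct the sample size.
- If the SD or the percentage was misprinted or rounded, print the value that was used.

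The cost is one sentence and, in the first case, a slightly less favourable figure. If at least 80% power is wanted with the printed inputs, 22 per arm are needed, since 21 gives 0.798. That means four more scans in total. Trial status and dissemination shows recruitment planned to June 2025, so the PET target could still be revisited at this version of the protocol.

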### Data management and monitoring

All personal information will be obtained at the eligibility assessment or from patient records in cases where participants are unable to provide the needed information. Pseudo-anonymized data from the neuropsychological tests, virtual reality test, questionnaires, interviews, and functional assessment will be registered in the REDCap database, which meets requirements from the Danish Data Protection Agency. Pseudo-anonymized raw paper data from neuropsychological tests are kept in a locked filing cabinet. Questionnaires and interviews are collected directly in REDCap. Data quality is ensured by score range restrictions on values for all outcomes, and all data for the primary and secondary outcome measures will be doublechecked prior to analyses. Signed consent forms as well as a list that matches participant ID numbers with personal information are kept separate from pseudo-anonymized data. The key matching participants’ personal information with their ID number will be deleted and consent forms maculated 10 years after study completion. At this point, all data will be completely anonymized. All trial authors will have access to the final trial dataset. If a participant is excluded or withdraws from the study, the reason for exclusion is documented in REDCap, along with information regarding any adverse events.

